### Data monitoring

There is no significant risk in the supplementation of probiotics, and adverse events or symptoms are rarely described in the literature; therefore, a data monitoring committee is not necessary. However any symptoms will be reported by the patients and considered in this research.

### Harms

In the treatment-adherence control worksheet it will be possible to write down any possible symptoms that may appear during the period. Also, patients will be advised that if they feel any symptom or discomfort during the treatment they will be free to stop.

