### Interventions

The patients will be randomized to an intervention group (probiotic) or a control group (placebo). Patients allocated to the intervention group will receive probiotic supplementation which consists of a 1-g sachet containing *Lactobacillus acidophilus* SD5221 (1 x 10^9^ CFU) + *Lactobacillus rhamnosus* SD5675 (1 x 10^9^ CFU) + *Lactobacillus paracasei* SD5275 (1 x 10^9^ CFU) + *Bifidobacterium lactis* SD5674 (1 x 10^9^ CFU), while those allocated to the control group will receive a 1-g sachet with an identical appearance (physical and organoleptic) containing polydextrose/maltodextrin as the placebo. Patients will be instructed to ingest two sachets daily with water at room temperature for a period of 24 weeks.

The patients will receive a spreadsheet to mark the intake of the sachets and write down any symptoms that may appear during the intervention period. Every 45 days, patients will be seen and adherence to treatment will be evaluated through the spreadsheet and by counting the sachets that were not consumed.

The participants will be instructed to advise the research team about the need to use any other non-routine medications, as some medications may alter the intestinal microbiota, and also to inform the team when they use a product that contains probiotics.

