#### Sarcopenia

Sarcopenia will be determined following the European Consensus [25] considering muscle mass, muscle strength, and physical performance.

Muscle mass will be measured by the body composition assessment. DEXA (The GE Medical Systems Lunar Prodigy densitometer, Chicago, IL, USA) will be used for body-composition assessment. Fat and lean masses will be determined for the whole body and for body regions (trunk and limbs), as previously described [34]. Electrical bioimpedance (Biodynamics450®, Plainview, NY, USA) will be used to measure the percentage of fat, lean mass, and phase angle. Patients should be fasting for 4 h, not drink alcohol and/or caffeine, not have exercised in the last 12 h, not take diuretics the day before the test, not have a pacemaker in situ, and not be pregnant or menstruating. Patients will be questioned about the presence of significant diarrhea at the time of the examination to exclude the possibility of dehydration [35].

Muscle strength will be evaluated by the handgrip strength (dynamometry). Patients should be seated with their elbow flexed at 90° to hold the dynamometer (Jamar, Duluth, MN, USA) at its maximum strength for 3 s. There will be three repetitions with an interval of 1 min with the dominant hand. The highest strength will be recorded in kgF for classification [36].

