#### Cardiovascular-risk assessment

Cardiovascular risk will be estimated by the Framingham Risk Score [42] and the Atherosclerotic Cardiovascular Disease (ASCVD) risk calculator [43].

All data will be included in the database filled out by the researchers, as well as in a physical agenda to log the attendance frequency of the participants. The patients will be contacted to be reminded about the guidelines and to confirm the visits. Subjects who discontinue treatment will also have their data treated at the end of this study.

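### Harms are collected by unsolicited, unstructured patient self-report, with no active enquiry stated for the 45-day visits, so some events may go unrecorded or be read late

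*Protocol article*

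**What the plan says.** All references are to the protocol article.

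- **Harms.** The collection route is the adherence sheet: "In the treatment-adherence control worksheet it will be possible to write down any possible symptoms that may appear during the period". Patients are also advised that "if they feel any symptom or discomfort during the treatment they will be free to stop".
- **Interventions.** The sheet is for marking sachet intake and for patients to "write down any symptoms that may appear during the intervention period". On the visits: "Every 45 days, patients will be seen and adherence to treatment will be evaluated through the spreadsheet", together with a count of unused sachets. Patients are also "instructed to advise the research team about the need to use any other non-routine medications".
- **Abstract, Methods.** Patients are instructed to report symptoms or side effects that relate to the sachets. A full history is taken at baseline and again at 24 weeks.
- **Data monitoring.** No monitoring committee is planned because risk is judged low. Symptoms are expected to come from the patients and to be taken into account.
- **Sarcopenia.** The only symptom question that staff are said to ask belongs to the bioimpedance measurement: "Patients will be questioned about the presence of significant diarrhea at the time of the examination to exclude the possibility of dehydration".
- **Cardiovascular-risk assessment.** Two general sentences appear here: "The patients will be contacted to be reminded about the guidelines and to confirm the visits" and "Subjects who discontinue treatment will also have their data treated at the end of this study".
- **Ancillary care.** Free hospital care is provided for intercurrent events or harm from taking part.

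**The concern.** Every stated route for a symptom to enter the trial record starts with the patient, apart from the diarrhea question, which serves another purpose. What gets recorded then depends on what each patient thinks worth writing down or telling the team. The Abstract's instruction covers only effects that the patient connects with the sachets. A blinded patient cannot judge that connection well, and may leave out an infection or a hospital contact that seems to have nothing to do with a food supplement.

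Two things are at stake. One is timeliness: an entry made soon after a visit may not be read until the next one. The other is the final harms report: a low symptom count could reflect good tolerability or little writing, and the stated method gives limited means of separating the two. Because a committee has been ruled out on grounds of low risk, patient reports are the main stated source of symptom data, so it is worth collecting them in a standard way.

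**Working it through.** **1. Is there a stated enquiry about adverse events?** Each route in the article, with what it can and cannot capture:

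| Route | Section | Started by | Limit |
|---|---|---|---|
| Symptom entry on the sheet | Interventions; Harms | Patient | Only what the patient chooses to write |
| Instruction to report | Abstract | Patient | Limited to effects linked to the sachets |
| Notice of non-routine medication | Interventions | Patient | Only events that need treatment |
| Diarrhea question | Sarcopenia | Staff | One symptom, asked to make the bioimpedance reading valid |
| Reminder contacts | Cardiovascular-risk assessment | Staff | Guidelines and visit confirmation; no symptom question stated |
| Repeat history | Abstract | Staff | Once, at 24 weeks; adverse events not among the listed contents |
| Hospital care | Ancillary care | Not stated | Provides care; no recording described |

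No row is a standard question about adverse events put to every patient. The Harms section lets patients stop because of a symptom, and the data of those who stop are kept. The article does not say that the reason for stopping is recorded.

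**2. How long could a worksheet entry wait?** The plan's own figure is a visit interval of 45 days (Interventions). Treatment lasts 24 weeks × 7 = 168 days.

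Assumption: visits on days 45, 90 and 135, and close-out on day 168. The close-out day is inferred from the 24-week duration.

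- Gaps between visits: 45, 45, 45 and 33 days.
- Longest wait: 45 days = 45/7 = 6.4 weeks = 45/168 = 26.8% of the treatment period.
- Mean wait, with onset uniform over the 168 days: (3 × 45²/2 + 33²/2)/168 = (3037.5 + 544.5)/168 = 3582/168 = 21.3 days.
- If close-out fell on day 180 instead, all four gaps would be 45 days and the maximum would be unchanged.

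These waits apply only to an entry that reaches the team by no other route. A spontaneous report, a reminder contact or a medication notice would shorten them.

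**3. How many events would be missed?** The article gives no symptom rate and no reporting rate, so no estimate is possible.

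**4. Who could still benefit from a change?** Trial status reports that 45 patients had started, against a planned 46, with recruitment expected to end in May 2019. A patient starting on 31 May 2019 would be treated until 15 November 2019 (31 May + 168 days). The number still on treatment is not given.

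**The case against.** The strongest objection is that this is a condensed article. Visit-level adverse-event questions and forms usually sit in the full protocol (here version 6.0), and the schedule in Fig. 1 is not available. Nothing in the Harms section is false, and nothing in it forbids asking. This lowers confidence and weight. It does not remove the point, because the Harms section is not silent: it names a route, and that route is passive.

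Four stronger readings are tempting, and the article does not support them.

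- **Reporting is optional.** A reader might infer this from the permissive wording under Harms. The Abstract says that patients are instructed to report, and Data monitoring expects them to. The accurate description is unsolicited and unstructured. That entries are free text is itself an inference.
- **The visits exclude symptoms.** The sentence under Interventions explains how adherence is assessed and does not say that nothing else happens. Staff hold the sheet with the symptom entries at every visit.
- **A sheet without symptoms says nothing.** The sheet also carries intake marks. Marked intake with no symptoms shows that the patient was using it, and a wholly blank sheet shows non-use. What remains uncertain is under-recording by patients who do use the sheet.
- **Events will typically wait 45 days.** That is the worst case, and it requires every other route to fail.

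It can also be said that a diary plus spontaneous reports, collected at regular visits, is a recognisable approach for a supplement judged low-risk, and that the remedy comes late. Both are fair, and both are reasons to rate the point low. A standard question at visits already planned is still a cheap improvement.

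**Conclusion.** The point holds as a minor one. The article's stated method for harms is patient self-report without prompting or structure, and it states no active enquiry about adverse events at the 45-day visits. Events thought minor or unrelated may go unrecorded. An entry not otherwise reported could wait up to 45 days, or about 21 days on average under the assumed visit days and uniform onset.

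A reader might infer that the trial's main result is compromised, or that data from patients who stop are lost. Neither follows. The primary outcome is an elastography measurement that does not depend on symptom reports, the article plans no between-arm test of harms, and data from those who stop are retained. The only gap there is that no recording of the reason is stated.

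Confidence is moderate, because the full protocol or the schedule figure may contain a visit question.

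**What to change.** 1. At each remaining 45-day visit and at close-out, blinded staff first copy the symptom entries from the worksheet. They then ask every patient the same short list (bowel symptoms, fever or infection, hospital contact, new treatment), whatever the patient believes the cause to be. For anyone who stops, record the reason. Keep the worksheet, because recall over 45 days has its own error.
2. Ask patients to contact the team between visits about infection, hospital care or a symptom that makes them stop, as they already do for non-routine medication.
3. Report the number and percent of patients with at least one event in each arm, showing elicited and worksheet events separately.

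If the full protocol already contains a visit symptom question, stating it in the Harms section meets the first step.

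**Cost.** A one-page form, a few minutes at visits already planned, and a small amendment; no new visits or staff.

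**Downside.** Symptom counts will rise in both arms, and ascertainment will be mixed because 45 patients had already started. Those who have finished will have worksheet data only, and those under way will have no elicited baseline. Showing the two sources separately keeps this visible.

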### Auditing

The research will be regularly reviewed by the responsible researchers and professors involved.

### Confidentiality

The data collected during the surveys will always be treated confidentially. The results will be presented together, without the identification of the participants.

### Ancillary care

In the event of any intercurrent events or damage resulting from the participation of the subjects in the survey, they will receive all necessary care, at no personal cost, at that hospital.

### Dissemination policy

During and after the survey, the ClinicalTrials.gov database will be replete with data. After completing the research and processing the data, an article will be written for later publication in an international journal for the dissemination of data and results.

## Discussion

This is the first double-blind, randomized clinical trial in NASH patients that will evaluate not only the repercussion of 24-week probiotic supplementation on the disease, the intestinal microbiota, and nutritional changes, but also sarcopenic parameters. This study will evaluate several parameters: nutritional, functional, physical, and laboratorial assessments, including tests used for diagnosis and follow-up (TLR-4 and CK-18), and evaluation of degree of liver fibrosis, intestinal permeability, microbiota composition, and cardiovascular risk.

Because NASH is a worrying disease, already considered one of the main indications for liver transplantation [3], it is important to investigate an adjuvant treatment for this disease. It is believed that treating dysbiosis by modulating the intestinal microbiota through probiotic supplementation may be beneficial for NASH patients. However, the studies remain heterogeneous from the point of view of intervention time and products and quantities of supplements used [17–19, 29, 45].

In this study, there is a research team, consisting of dietitian nutritionists, hepatologists, and undergraduate students, committed to the appropriate selection of patients and all data collection. As previously mentioned, the probiotics were donated for this research. We believe that the findings from this study will be generalizable to populations outside Brazil, considering its high methodological quality (based on similar studies), which includes the randomized sample composed of patients found in routine clinical practice.

## Trial status

The study is in the data collection phase. Recruitment started in March 2018 and is predicted to end in May 2019. Forty-five patients have started the study protocol and additional patients are being recruited. The current protocol is version 6.0, created in September 2017 and approved by the Ethics Committee of Hospital de Clínicas de Porto Alegre in October 2017, before randomization.

## Data Availability

Access to data will be controlled by the chief investigator. Donors of probiotics and placebos will have access only to published data. Trial participants or their proxies are provided with assurances about the maintenance of privacy and confidentiality in the informed consent. Participating patients will have access to the results of the routine examinations that are in their medical records, and the other tests will be available from the investigators according to the patients’ interest and request.

## Abbreviations

FTSTS: Five-times sit-to-stand test
kPa: Kilopascals
NAFLD: Non-alcoholic fatty-liver disease
NASH: Non-alcoholic steatohepatitis
PCR: Polymerase chain reaction
TLR: Toll-like receptor
